Although rTMS improves the neuroplasticity of the brain, the improvement of cognitive function is frequently limited to some extent. It is necessary to combine other methods, such as cognitive training, to boost cognitive functions. A research about the combination of rTMS and motor rehabilitation has testified that the intervention based on improving cortical plasticity is more effective than other groups. However, a recent systematic review on the improvement of working memory in schizophrenia suggests that the combination of rTMS and working memory training (WMT) may improve the working memory ability [3].

So far, traditional cognitive training, especially working memory training, has small to medium effect on the improvement of cognitive function. Although standard rTMS can improve the neural plasticity, there are some limitations, such as inefficiency, time-consuming, and lack of strong evidence of cognition improvement. To sum up, we hypothesize that there is a joint enhancement effect of combination between iTBS and WMT, i.e., the combination training mode of “preheating (iTBS stimulation changes the activity of working memory-related brain regions) and ironning (working memory training).” At present, there is no relevant research report to explore whether and how the joint intervention will have a combined effect on improving cognitive function, especially working memory, in schizophrenic patients.

To our knowledge, this is the first study to test the efficacy of a combination of iTBS and WMT on working memory and other cognitive functions of schizophrenia using a double-blinded, randomized controlled trial design. In order to evaluate the efficacy of invention, we will use behavior outcomes (such as neuropsychological assessment) and neuroplasticity outcomes (such as brain microstructural index) combining with neuroimaging indexes. This study will provide scientific evidence for improving cognitive deficits, especially working memory deficits, and elucidate the neuroplasticity mechanism of iTBS stimulation combined with working memory training.

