## Methods/design

### Study design

The study will be implemented as a double-center, double-blinded, randomized trial. This was registered under Chictr.org.cn (ChiCTR1900023405). This study will be reported in accordance with both the Consolidated Standards of Reporting Trials (CONSORT) statement and the CONSORT statement for non-pharmaceutical interventions [26, 27].

The primary objective is to explore the facilitation (enhancement) effects of iTBS-induced neuroplasticity changes on the direct and migration effects of working memory training on the cognitive function of schizophrenia. The secondary objectives are to investigate the effects of iTBS, working memory training on brain functional and structural plasticity in schizophrenia, and the facilitation (enhancement) of iTBS on brain functional and structural plasticity induced by working memory training.

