### Randomization

Participants will be randomly allocated to four groups: study group (iTBS+WMT), WMS control group (iTBS+SRT), iTBS control group (sham iTBS+WMT), and placebo control (sham iTBS+SRT) in a ratio of 1:1:1:1, with stratification. After patients have given their consent form, randomization will be performed by an independent and professional statistician who is blinded to the patient interventions using block randomization in R Programming (Mathsoft company, USA). Each center has its own enrollment time as a compatibility factor, and 8 patients in the vicinity of the enrollment time are used as a block. There are 15 blocks (total 120 patients) in Beijing Huilongguan Hospital and 10 blocks (total 80 patients) in Shenyang Anning Hospital. Then, the sealed randomization codes and intervention number are sent out to each hospital. Blinding will have to be broken only if a patient needs emergency handling. Once in this way, the participant will be managed as off-trial.

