### Sample size

The hypothesis is 77.2% response rate in the cognitive training group and 41.4% in the control group on our preliminary studies [32]. The difference between the two groups was improved about 35.8%, as the basis for calculation. With a statistical power of 80% and a significance level of 5%, the minimum sample size of 28 subjects is required in each group. With our previous research experience, we allow for a maximum dropout rate of 20%. The study adopts the block randomization to divide into groups with 8 patients in each block. The actual minimum sample size of each group was 34 cases. Combining each center clinical states, Beijing center inclusion number has been set to 120 patients to participate into this research and Shenyang center has 80 patients.

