### Statistical analysis

The analysis will be conducted on the basis of the intent-to-treat (ITT) principle. Some descriptive analysis of the data gathered during each assessment will be carried out precisely until the final assessment. Special time points for analysis are the baseline, end of iTBS or sham iTBS sessions, and 3 and 6 months after the final treatment. Median and range describe continuous variables, and frequencies and percentages describe qualitative variables.

We will accept a significance level of 5% (*P* < 0.05) corrected for multiple comparisons when needed. To assess our primary endpoint criterion, i.e., cognitive performance changes on the task, outcomes at four time points will be compared using repeated measurement analysis of variance of variance with time (baseline, ending, and 3 and 6 months after the final treatment) and group (study group (iTBS+WMT), WMS control group (iTBS+SRT), iTBS control group (sham iTBS+WMT), and placebo control (sham iTBS+SRT)) as factors. Further comparison between the two groups can show the simple iTBS effect, the simple WMT effect, and the facilitation effect of iTBS on WMT. Sensitivity analyses will explore the impact of imputation of data losses including loss to follow-up and dropout.

In the case that the data do not meet the normal distribution assumption, the non-parametric Mann-Whitney test will be used to compare performance improvements between four groups. SPM will be used to analyze imaging data to detect any changes in brain function and structure caused by cognitive training.

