## Discussion

To our knowledge, this is the first trial aiming to solve the problem of limited overall effect and migration effect of working memory training in schizophrenia by performing professional training, which is based on changing the neuroplasticity of working memory-related brain areas through iTBS primitively.

This trial has several advantages. First, this study use iTBS stimulation, which is currently a well-evidentiary and efficient way to alter the plasticity of the brain, as a tool to regulate the functional state of brain regions before working memory training. The effects of iTBS on brain function and structural plasticity in schizophrenia were investigated by structural and functional MRI.

Second, we hypothesize that iBTS stimulation, which will be able to alter brain plasticity, will facilitate (enhance) the clinical effects of working memory training on improving cognitive function of schizophrenia? This is a key issue in the study of WMT mechanism, that is, whether the way of “preheating (iTBS stimulation activates local neuronal activity first) and then ironning (working memory training)” can make “iron better tempered” (the changes of brain function and structure are more significant). In our study, the WMT control group (iTBS+SRT) and iTBS control group (sham iTBS+WMT), were set up to compare with the study group, respectively, and to analyze the differences of brain plasticity, to explore whether the training of “preheating and then ironning” (iTBS+WMT) is superior to that of “ironning without preheating” (sham iTBS+WMT) and “ironning without preheating” (iTBS+SRT) in changing the neuroplasticity (function and structure) and to provide a scientific basis for exploring ways to enhance the neuroplasticity of the brain and improve its function.

Another advantage of this trial is to explore the migration effect, that is, whether training can improve untrained cognitive ability as well as related-cognitive processing ability, such as whether it can improve logical reasoning ability after working memory training? The training for the normal youngs suggests that working memory training alone can improve memory function and fluid intelligence, thus verifying the existence of migration effect of working memory training. However, there are few studies on whether the migration effect occurs in schizophrenia, and this study makes up for the shortcomings in this area.

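### Facilitation of WMT by iTBS, the primary objective, is assigned to a two-group comparison, which cannot separate it from an additive iTBS effect; the difference-in-differences contrast should be named

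*Protocol article*

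**What the plan says.** The Study design section sets the target: "The primary objective is to explore the facilitation (enhancement) effects of iTBS-induced neuroplasticity changes on the direct and migration effects of working memory training". The Background states the hypothesis in similar terms ("we hypothesize that there is a joint enhancement effect of combination between iTBS and WMT"), and the Discussion asks whether iTBS "will facilitate (enhance) the clinical effects of working memory training on improving cognitive function of schizophrenia".

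The Randomization section allocates patients to iTBS+WMT, iTBS+SRT, sham iTBS+WMT and sham iTBS+SRT "in a ratio of 1:1:1:1, with stratification".

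For the primary endpoint, the Statistical analysis section says that "outcomes at four time points will be compared using repeated measurement analysis of variance of variance with time" and a single four-level group variable as factors. It then adds: "Further comparison between the two groups can show the simple iTBS effect, the simple WMT effect, and the facilitation effect of iTBS on WMT". The Discussion describes the two single-active arms in the same pairwise way, there for imaging outcomes: they "were set up to compare with the study group, respectively, and to analyze the differences of brain plasticity". Neither an iTBS-by-WMT interaction nor an equivalent contrast of all four arms is named anywhere.

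The Sample size section rests on response rates of 77.2% with cognitive training and 41.4% in control. That is one training-versus-control difference.

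**The concern.** Whether iTBS enhances the effect of working memory training is a question of effect modification: is the gain from WMT over SRT larger after real iTBS than after sham? Answering it needs all four arms. A comparison of two arms answers something else, namely whether one regimen beats another.

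If iTBS improves cognition by the same amount whichever training follows, iTBS+WMT will still outperform sham iTBS+WMT, although iTBS has facilitated nothing. Read as the article instructs, that result would be reported as facilitation. What is at stake is a wrong answer to the primary question from data that could have answered it correctly.

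**Working it through.** **The plan's own figure.** With p₁ = 0.772, p₂ = 0.414, mean 0.593 and difference 0.358, at two-sided 5% and 80% power (sidedness is assumed, as the article does not state it), the usual two-proportion formula is

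n = [1.960·√(2·0.593·0.407) + 0.842·√(0.772·0.228 + 0.414·0.586)]² / 0.358² ≈ 28.4.

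The arcsine version gives 28.05. The stated 28 per group therefore reproduces to within rounding, and 28 × 1.2 = 33.6 gives the stated 34. The figure is sound for what it is, a two-group comparison. It does not concern an interaction.

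**What each contrast estimates.** Let a be the iTBS effect under SRT, b the WMT effect under sham, and g the facilitation (interaction). The arm means, relative to sham iTBS+SRT, are:

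| Arm | Mean |
|---|---|
| sham iTBS+SRT | 0 |
| iTBS+SRT | a |
| sham iTBS+WMT | b |
| iTBS+WMT | a + b + g |

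- iTBS+WMT − sham iTBS+WMT = a + g
- iTBS+WMT − iTBS+SRT = b + g
- (iTBS+WMT − sham iTBS+WMT) − (iTBS+SRT − sham iTBS+SRT) = g

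No single pair returns g. The third contrast does.

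**How often the pair misleads when g = 0.** The planned 200 patients give 50 per arm, or 40 after 20% dropout. Assumptions: one post-treatment score with SD 1, two-sided 5% t-tests, no multiplicity correction. The article gives no iTBS effect on MCCB, so a is shown as a range:

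| Assumed a (SD) | iTBS+WMT vs sham iTBS+WMT significant, 50 per arm | 40 per arm |
|---|---|---|
| 0 | 5% | 5% |
| 0.1 | 8% | 7% |
| 0.2 | 17% | 14% |
| 0.3 | 32% | 26% |
| 0.4 | 51% | 42% |

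Requiring superiority over both single-active arms does not cure this. With a = b = 0.4 and g = 0 it still occurs in about 34% of trials at 50 per arm and 26% at 40. In simulation the interaction test rejects in about 5% throughout.

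**Precision of the correct contrast.** A pair has variance 2·SD²/n and the four-arm contrast 4·SD²/n, so the standard error is √2 = 1.41 times larger. At 50 per arm the standard errors are √(2/50) = 0.20 and √(4/50) = 0.283. The effect detectable with 80% power is 2.80 × 0.20 = 0.56 SD for a pair and 2.80 × 0.283 = 0.79 SD for the interaction (0.63 and 0.89 at 40 per arm).

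The Background cites cognitive-training effects of 0.38 overall and 0.29 for working memory. These are not interaction effects and serve only as a yardstick. Interaction power at 50 per arm is Φ(0.38/0.283 − 1.96) = 27% for 0.38 SD and 17.5% for 0.29 SD. For 80% power at 0.38 SD, n = 4 × 2.80²/0.38² ≈ 218 per arm.

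**The case against.** The strongest reply is that facilitation may mean no more than add-on benefit. The Abstract's discussion glosses the aim as patients gaining more from the combination, and the main Discussion speaks of superiority over each single-active arm (for imaging outcomes). A pairwise contrast answers that question. This shows that the wording is loose, but it does not remove the problem. The stated objective and hypothesis concern enhancement of the training's effect, and the Statistical analysis section lists facilitation separately from the simple iTBS effect.

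A second reply is that the phrase about the two groups is loose English, that it names no particular pair, and that exact contrasts can wait for the SAP. It is true that no pair is named. But the article does not leave the matter open: it says that a two-group comparison shows facilitation, and that fails for every pair and for both single-active pairs taken together.

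A third reply concerns size, and part of it stands. The false-claim rate depends on iTBS having an effect of its own. If a = 0, the pair with sham iTBS+WMT does estimate g. The Background reports that 10-Hz rTMS did not beat sham on cognition, so a small a is plausible. The article also allows correction for multiple comparisons when needed: an assumed Bonferroni correction for three pairs lowers 51% to about 34% at 0.4 SD, and 17% to about 8% at 0.2 SD.

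Two further inferences are tempting and are not supported. One is that coding group as one four-level factor is itself an error. In a complete 2×2, that factor crossed with time is the same saturated model as iTBS × WMT × time, and the needed contrast can be taken from its cell means. The other is that pairwise comparisons waste data compared with pooling over the factorial margins. The article asks for simple effects, and marginal effects equal simple effects only when there is no interaction, which is the opposite of what the trial hypothesises.

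**Conclusion.** The point holds. The algebra needs no outside assumption: the comparison that the article assigns to its primary objective estimates a simple effect plus the interaction, so it can indicate facilitation when the effects only add. The size is conditional. At 50 per arm the rate of such false claims runs from 5% with no iTBS effect to about 51% with an assumed 0.4 SD, before any multiplicity correction. The article gives no figure that fixes where in this range the truth lies, so a reader should not infer that a false claim is the likely outcome.

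Nor should a reader infer that the sample size arithmetic is wrong. It reproduces, but it does not power the facilitation test. The interaction power figures assume a single post-treatment score with SD 1. Baseline adjustment or repeated measures would raise them by an amount that the article does not allow one to compute.

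**What to change.** - Keep the group-by-time model. Name the contrast (iTBS+WMT − sham iTBS+WMT) − (iTBS+SRT − sham iTBS+SRT), on change from baseline to end of treatment, as the test of facilitation.
- Report iTBS+WMT versus sham iTBS+WMT and versus iTBS+SRT as superiority of the combination over each single intervention, not as facilitation.
- State the precision expected for the facilitation contrast at 50 and 40 per arm, and do not present the existing sample size calculation as powering it.

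The cost is wording and analysis code; no new data are needed. The price is candour about power: the named contrast has 1.41 times the standard error of a pair, and a non-significant result would say little about interactions well below 0.8 SD. Its estimate should therefore be reported with a confidence interval.

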### Participants

Two hundred patients with schizophrenia will be recruited on fulfillment of the inclusion criteria. The patients will be randomly allocated into four groups, i.e., the study group (iTBS+WMT), WMS control group (iTBS+ Simple Response Training, SRT), iTBS control group (sham iTBS+WMT), and placebo control (sham iTBS+SRT). Patients will be recruited in two specialty neurostimulation centers at Beijing Huilongguan Hospital, Shenyang Anning Hospital.

This trial has been approved by the local Ethics Committee and followed close to the principles of the Declaration of Helsinki (version 2004). And Standard Protocol Items: Recommendations For Interventional Trials (SPIRIT) Checklist is detailed in additional file according to requirements. All of the patients sign a written consent form in order to take part in the study, after acquainting the aim and procedures.

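### The non-normality fallback assigns a two-sample test, Mann-Whitney, to a four-group comparison and leaves the comparisons that replace the primary analysis unspecified

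*Protocol article*

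**What the plan says.** All of the analysis text is in the Statistical analysis section of the protocol article.

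- Primary analysis: "outcomes at four time points will be compared using repeated measurement analysis of variance of variance with time" (four levels) and group (four levels) as factors.
- Follow-up: "Further comparison between the two groups can show the simple iTBS effect, the simple WMT effect, and the facilitation effect of iTBS on WMT".
- Multiplicity: "We will accept a significance level of 5% (*P* < 0.05) corrected for multiple comparisons when needed".
- Fallback: "In the case that the data do not meet the normal distribution assumption", then "the non-parametric Mann-Whitney test will be used to compare performance improvements between four groups".

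The fallback names no four-group rank test, no list of pairs and no handling of the three post-baseline visits.

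Two other sections matter. Under Study design, "The primary objective is to explore the facilitation (enhancement) effects of iTBS-induced neuroplasticity changes on the direct and migration effects of working memory training". Under Randomization, the four arms cross real or sham iTBS with WMT or simple response training (SRT), "in a ratio of 1:1:1:1, with stratification".

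**The concern.** The sentence names a specific test for a specific comparison, and the two do not fit. This is a method stated wrongly, not a detail left to an analysis plan, and nothing else in the article repairs it.

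It matters because the sentence governs the primary endpoint. The time-by-group model gives an overall comparison of the four arms across visits. Its four-level group factor can also carry the 2 x 2 interaction contrast, although the article does not name that contrast. Once the fallback is triggered, both are gone, and the analyst must decide after seeing the data which pairs to test, at which visits and with what correction. The switch depends on a check of the observed data, so the form of the primary test is not fixed in advance.

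**Working it through.** No figure in the article is in dispute here. The sample-size calculation compares two response rates and does not enter this point.

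**Inputs.** Four arms at 1:1:1:1 (Randomization). For the total, "Two hundred patients with schizophrenia will be recruited on fulfillment of the inclusion criteria" (Participants), so 200/4 = 50 per arm. Dropout of up to 20% (Sample size), so 50 x 0.8 = 40 per arm. Alpha 0.05; the article does not say whether it is two-sided, and two-sided is assumed. It gives no SD or effect size for the MCCB, so the effects below are assumptions: 0.3, 0.4 and 0.5 SD.

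**Step 1: how many tests the fallback implies.** Pairs among four arms: 4 x 3 / 2 = 6. If repeated at three post-baseline visits: 6 x 3 = 18 tests per score.

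**Step 2: familywise error for six pairs at one visit.** If the tests were independent and uncorrected: 1 - 0.95^6 = 26.5%. They share arms, so the true figure is lower. Simulation under no effect (3,000 runs per setting, 40 or 50 per arm, normal or lognormal errors):

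- six uncorrected Mann-Whitney tests: 20.0% to 21.1%
- the same six at 0.05/6 = 0.0083 (Bonferroni): 3.5% to 4.2%
- one Kruskal-Wallis test on four arms: 4.6% to 5.2%

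**Step 3: what a two-arm comparison estimates.** Let A = iTBS+WMT, B = iTBS+SRT, C = sham iTBS+WMT, D = sham iTBS+SRT. Let i be the simple iTBS effect, w the simple WMT effect and x the facilitation, meaning the extra WMT gain when iTBS is real. Relative to D:

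- A = i + w + x, B = i, C = w, D = 0
- A - C = i + x
- A - B = w + x
- (A - B) - (C - D) = (w + x) - w = x

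Only the last line isolates x, and it needs all four arms. The simulated interaction test was L / sqrt(sum of the four variances / n), with L = mean A - mean B - mean C + mean D, on 4n - 4 degrees of freedom.

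**Step 4: rejection rates with x = 0 and i = w** (normal errors, 1,500 runs, unadjusted 5% level):

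| n per arm | i = w (SD) | Mann-Whitney A v C | A v C and A v B both significant | Interaction contrast |
|---|---|---|---|---|
| 50 | 0.3 | 30.9% | 16.8% | 5.8% |
| 50 | 0.4 | 48.5% | 33.6% | 5.1% |
| 50 | 0.5 | 67.1% | 53.2% | 4.9% |
| 40 | 0.3 | 25.1% | 12.0% | 4.8% |
| 40 | 0.4 | 41.1% | 24.5% | 4.3% |
| 40 | 0.5 | 57.7% | 40.3% | 5.6% |

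The A v C rejections are correct detections of an iTBS effect. They become errors only if reported as facilitation.

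**Step 5: the case in which the fallback would apply.** With strongly skewed (lognormal) errors and the same additive shifts, Mann-Whitney A v C rejected in 86.6% to 99.9% of trials. The mean-based interaction contrast stayed at 3.5% to 5.7%. At these sample sizes, that degree of non-normality was no reason to abandon the interaction contrast. Simulation error is about 0.6 points at a true 5% with 1,500 runs: sqrt(0.05 x 0.95 / 1,500) = 0.0056.

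**The case against.** The sentence can be read charitably as pairwise Mann-Whitney tests, corrected for multiplicity. That is a valid procedure and matches the article's own two-group follow-up. A condensed article may leave the pairs and the correction method to the analysis plan. Much of this stands, and it rules out several stronger inferences that a reader might draw.

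- **That the fallback carries a 20% familywise error.** The same section provides for correction when needed. The 20% describes an uncorrected plan, which the article does not state. What stands is that the fallback sentence does not tie itself to any correction.
- **That facilitation could not be tested at all.** The article says two-group comparisons can show it, and the Discussion sets the study group against each single-component control when comparing brain plasticity. A pairwise Mann-Whitney can test such contrasts. It cannot distinguish x from i or w, but the two-group follow-up after the ANOVA has the same limit when normality holds, so this is not harm peculiar to the fallback.
- **That adjustment for baseline or centre is lost.** The planned ANOVA has only time and group as factors, so there is no covariate to lose. The fallback compares improvements, which reads as change scores and so takes account of baseline by differencing.
- **That normality would be judged on raw scores.** The text does not say so; it may mean the model's residuals.

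The consequence is also conditional on the rule being triggered, and nothing in the article gives the chance of that. Still, the charitable reading has to be supplied by the reader. The words give a two-sample test to four groups and say nothing about time.

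**Conclusion.** The sentence is wrong as written. One Mann-Whitney test cannot compare four arms. If the rule is triggered, the primary analysis loses its overall four-group test, its time factor and any place for the iTBS by WMT interaction contrast, and becomes a set of pairwise rank tests still to be chosen.

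The size depends on what is then done. Six pairs at one visit give about 20% familywise error without correction and about 4% with Bonferroni. If iTBS+WMT against sham iTBS+WMT is taken as the facilitation test, additive effects alone make it significant in 31% to 67% of trials at 50 per arm (25% to 58% at 40), against about 5% for the interaction contrast. These figures rest on assumed effects of 0.3 to 0.5 SD, normal errors, a two-sided 5% level and facilitation understood as a 2 x 2 interaction. The definite finding is an unworkable fallback rule for the primary endpoint; the documents do not support a claim of uncontrolled error or of a trial unable to address facilitation.

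**What to change.** Preferred: remove the rule that lets a normality check replace the primary test. Keep the planned time-by-group model and name the interaction contrast (A - B) - (C - D) on change from baseline. If residuals are clearly non-normal, base inference on robust standard errors or on a bootstrap or permutation test. Report rank methods only as sensitivity analyses.

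Minimum: replace the sentence with a Kruskal-Wallis test on change scores at each post-baseline visit, followed by pairwise Mann-Whitney tests with the pairs and the multiplicity correction named. This makes the fallback workable, but it still provides no interaction test.

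The cost is a short rewording before unblinding and a little more analysis work. No change to sample size or data collection follows.
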